## Methods

### Study Design

This is a 2-group, parallel pRCT with embedded personal network study comparing: (1) Intervention: Helpers Stay Quit training, and (2) control: quitline postabstinence follow-up usual care. The primary outcome is smoking status at 6 and 12 months. The purpose of the pRCT is to assess if a novel behavioral intervention (Helpers Stay Quit) overall has any effect on relapse in newly abstinent smokers following standard quitline treatment compared to quitline usual care, in real-world conditions of serving state quitline client populations. Relapse and the number of helping conversations will be assessed using a text survey weekly for the first 6 months and biweekly for months 7‐12. The prestudy quitline treatment, quitline referral, study recruitment, screening, consent, and prerandomization and run-in period are depicted in Figure 1. The postrandomization study intervention exposure, assessment intervals, and qualitative interviews are depicted in Figure 2.

**Figure 1. F1:**
[figure not shown]
Timeline for recruitment, screening, consent, and prerandomization run-in for the helpers stay quit pragmatic randomized controlled trial and embedded personal network assessment (PNA).

**Figure 2. F2:**
[figure not shown]
Postrandomization study timeline and data collection schedule for the Helpers Stay Quit (HSQ) pragmatic randomized controlled trial.

### Ethical Considerations

The Helpers Stay Quit study was approved by all participating institutions’ institutional review boards (IRBs), including the Combined Multiple Institution Review Board of the University of Colorado (21‐4624), Arizona Department of Health Services (HSRB # 23‐0016), Kentucky Cabinet for Health and Family Services IRB (CHFS-IRB-DPH-FY23-35), Massachusetts Department of Public Health (MDPH IRB 00000701), Ohio Department of Health Human Subjects IRB (2023‐21), Pennsylvania Department of Health IRB (2022‐065), and Utah Department of Health and Human Services IRB (686).

The IRBs for Texas A&M University, University of Florida, Kansas Department of Health and Environment, Michigan Department of Health and Human Services, and the Vermont Agency of Human Services each determined that the Helpers Stay Quit study could be implemented without additional IRB review.

Informed consent was conducted by telephone; participants could see the consent form on a screen, could electronically sign the form, and were emailed a copy of their signed consent. As part of the informed consent process, participants were read paragraphs from the consent form as shown in Multimedia Appendix 1.

Study participants’ confidentiality is protected by the following measures: all study participants are assigned a numerical study ID. The linking file that contains both study ID and participant-identifying information (name, address, telephone number, and email) is stored on a secure server in a physically secured server room. The linking file is only accessible by research staff employed by the University of Colorado. Data files shared with co-investigators, statisticians, and analysts are deidentified.

Participants completing every protocol activity and qualifying for every incentive could receive a total of US $419. A breakdown of the study protocol items and their compensation rates is as follows: baseline (US $20), social network assessment 1 (US $25), training (US $40), incentive for completing training within two weeks (US $10), 3-month survey (US $20), 6-month survey (US $20), 9-month survey (US $20), 12-month survey (US $20), bonus for completing all 4 surveys (US $5), social network assessment 2 (US $25), qualitative personal network interview (US $30), weekly text survey (24 total; US $4 each), biweekly text survey (12 total; US $4 each), 6-month follow-up specimen completion incentive (US $15), 12-month follow-up specimen completion incentive (US $15), and maximum completion bonus for completing all study activities (US $10).

### Participant Recruitment, Eligibility, Enrollment, and Randomization

#### Recruitment

Participants are referred from state quitlines based on a prescreening algorithm programmed into the coaching platform that identifies potentially eligible quitline callers self-reporting abstinence during their third, fourth, or fifth coaching call, and interested in being referred to the study. Upon referral from the quitlines, study staff contact participants via telephone to screen for initial study eligibility, provide the participants with a detailed explanation of the study’s purpose and procedures, and obtain electronic informed consent from those who are eligible and wish to proceed to the prerandomization run-in period.

##### Eligibility Criteria

The eligibility criteria are shown in Textbox 2.

Textbox 2.Eligibility criteria.Inclusion criteria:Participants are aged 18 years and older.Abstinent from smoking for between 14 and 60 days per self-report.Primary tobacco use is cigarettes.Has access to the internet via computer or mobile device.Self-described proficiency with English.Willing and able to send and receive weekly text messages using personal mobile phone.Will allow the quitline to share its client data with the research team.Willing to complete online surveys at baseline, 3, 6, 9, and 12 months.Willing to self-collect dried blood spot for biological confirmation of smoking status and send back to the research team.If assigned to the Helpers Stay Quit condition, willing to complete the training within 14 days.If selected, willing to participate in a qualitative interview.Willing to forego any other training for tobacco cessation intervention or support (ie, to become a cessation counselor or facilitator or support person, eg, “quit buddy”) for the duration of their study enrollment.Exclusion criteria:Any previous exposure to Helpers Stay Quit or other cessation training in the previous 2 years.Relapse within 10 days (run-in phase) before enrollment and randomization.Participants are not precluded from continuing their personal tobacco cessation activities with quitline or other services or aids (eg, support groups, medication, etc).Concomitant use of cessation aids is tracked while participants are enrolled in the study via online surveys (baseline, 3, 6, 9, and 12 months, and weekly or biweekly text surveys).

### Prerandomization Run-in/Baseline Measures

A major strength of the Helpers Stay Quit study design is the clear separation of quitline cessation treatment from the Helpers relapse prevention intervention. This separation is maintained by requiring that all participants attest to their continued abstinence immediately before randomization. After initial study eligibility screening, consented participants have up to 10 days to complete study run-in baseline measures, which include a survey of cognitive and emotional measures (Table 1) and a personal network assessment (PNA). Those who fail to complete run-in baseline procedures are not randomized into the study. Immediately before randomization, participants attest to their continued abstinence (7-day point prevalence; Figure 1).

**Table 1. T1:** Data collection schedule for the Helpers Stay Quit study pragmatic randomized controlled trial.

Data collected	Baseline	Training pre-post	Weeks 1‐24	3-month follow-up	6-month follow-up	Weeks 25‐52	9-month follow-up	12-month follow-up	Dyad qualitative interviews, months 5‐12
Tobacco use or abstinence (1° outcome)	✓		✓	✓	✓	✓	✓	✓	
Cotinine					✓			✓	
Helping conversations (2° outcome)			✓	✓	✓	✓	✓	✓	
Helping conversation content				✓	✓		✓	✓	
Personal network assessment	✓							✓	
Cessation knowledge		✓							
Cessation fatigue	✓			✓	✓		✓	✓	
Abstinence Related Motivational Engagement-Short Form	✓			✓	✓		✓	✓	
Smoker or quitter identity	✓			✓	✓		✓	✓	
Smoker group identity	✓			✓	✓		✓	✓	
Residual attraction or vulnerability to smoking	✓			✓	✓		✓	✓	
Situational smoking abstinence self-efficacy	✓			✓	✓		✓	✓	
Proactive Coping Inventory	✓			✓	✓		✓	✓	
Patient Health Questionnaire-4	✓			✓	✓		✓	✓	
Qualitative aspects of network change, continuity									✓

### Randomization

Participants are randomized using stratified block randomization to ensure balance between study arms within key subgroups. Randomization is stratified by quitline and race and ethnicity (categorized as non-Hispanic White, Hispanic, non-Hispanic Black, and other). Within each stratum, participants are assigned to intervention or control groups in random block sizes of 4 and 6. The use of variable block sizes minimizes the predictability of treatment allocation while maintaining approximate balance in group assignments throughout the enrollment process. Randomization is implemented using a computer-generated randomization schedule prepared by the study biostatistician and concealed from study personnel involved in participant recruitment and assessment.

### Intervention and Comparison Conditions

#### Helpers Stay Quit Intervention

The Helpers Stay Quit intervention is a web-based tobacco cessation brief intervention training designed specifically for lay community members interested in helping someone in their lives quit tobacco. The multimedia, interactive, web-based training emphasizes a tobacco user–centered, nonconfrontational approach to encouraging others to quit. Helpers Stay Quit trainees (ie, “Helpers”) learn how to offer a 4-step “helping conversation” to encourage quitting and use of evidence-based cessation aids (eg, cessation medications, and quitlines), and to offer referrals to quitlines and reliable information sources (eg, pharmacists, National Cancer Institute’s SmokeFree website). The 4 steps of a helping conversation parallel the 4 core training modules of Helpers Stay Quit (awareness, understanding, helping, and relating), incorporating key components of the Public Health Service guideline’s recommended 5As [39].

A key learning objective of Helpers Stay Quit training is for trainees to learn how to manage their own expectations for the process and outcome of a helping conversation. For example, they cannot “make” anyone quit, but they can offer nonjudgmental encouragement and support and information about effective cessation aids. Helpers are taught to avoid nagging, confrontation, or pushing anyone to quit. The helping conversation focuses on encouraging behavior change that is aligned with the tobacco user’s current willingness and readiness to take any action toward quitting. Helpers Stay Quit includes content on evidence-based cessation aids and sources of reliable information about quitting. The training includes video role-plays of helping conversations and testimonials of current and former tobacco users and “concerned others” to illustrate core concepts. Learning activities prompt personal reflection and require application of new knowledge through scenario-based quizzes and decision-testing (eg, tobacco use, benefits of quitting) and skills (eg, recognition of appropriate use of communication techniques, identifying optimal or suboptimal responses to helping conversation interactions). Participants also have access to downloadable “Helpers tools,” which are simple brochures on topics such as “Thinking of Quitting” and “Benefits of Quitting.” The training takes approximately 2.5 hours to complete and includes a pre- and posttest and a downloadable certificate for successful training completion.

#### Quitline Usual Care Comparison

Quitline posttreatment usual care for our participating quitlines is to contact clients for follow-up assessment of abstinence at 7 months after enrollment in services, regardless of the number of calls completed. If the client has relapsed, the quitline attempts to reengage the client in cessation services. The participating quitlines each have a website that accompanies and complements their telephonic services. The websites contain information about tobacco use, tobacco cessation, descriptions of telephonic quit coaching services, and how to access quit coaching and cessation medications offered by the quitline. None of the quitline websites offer information specific to how to help others quit tobacco.

### Measures and Data Collection for Pragmatic Randomized Controlled Trial (pRCT)

#### Quitline Client Data

Participants consent for their quitline data to be shared with the study team including demographics (age, gender, and race and ethnicity), education, income level, presence or absence of behavioral health or chronic disease conditions, zip code, detailed tobacco use history and current use, time to first cigarette, use of electronic nicotine delivery systems, cessation medications provided and used, and number of quitline coaching calls completed.

#### Relapse Status (Primary Outcome) and Helping Conversations (Secondary Outcome)

Smoking or other tobacco use, electronic nicotine delivery device use, use of cessation aids, and helping conversations are assessed by online surveys at baseline, 3, 6, and 12 months, and by weekly text message surveys for months 1‐6, then biweekly text surveys for months 7‐12. Relapse is defined as (1) any smoking on 7 consecutive days or (2) smoking at least once each week over 2 consecutive weeks. Multiple relapses are defined as relapsing, reporting being quit (7-day point prevalence), and then subsequently reporting smoking again. Offers of helping conversations are assessed by baseline survey and weekly text message surveys (months 1‐6), then biweekly text surveys (months 7‐12). A 5-point Likert scale queries confidence in helping conversations, for example, talking to others about quitting smoking. Content of typical helping conversation (eg, setting quit date, quit plan, cessation medication, quitline referrals, and avoiding relapse) is queried via a yes or no checklist at baseline, 3, 6, 9, and 12 months (Table 1).

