### Research Objectives

This study is designed to assess the effect of Helpers Stay Quit training on the proportion and duration of participants maintaining abstinence or relapsing over time and on participants’ personal network structure and interactions related to smoking and smoking cessation. Primary and secondary research questions are as described in study-specific aims (Textbox 1).

Textbox 1.The Helpers Stay Quit study-specific aims.Aim 1: Using a 2-group, pragmatic randomized, controlled trial (pRCT; N=940) in which abstinent smokers (2-6 weeks abstinent) are randomized to the Helpers Stay Quit intervention or quitline follow-up usual care, to evaluate the effectiveness of Helpers Stay Quit on:Smoking status (30-day and 7-day point prevalence abstinence) at 6- and 12-month intervals (primary outcome).The number, timing, and duration of participants’ lapses and relapses to smoking (secondary outcome).Rates of participants’ self-reported delivery of helping conversations to other tobacco users (secondary outcome).Aim 2: embed a mixed methods social network study into the pRCT to examine the Helpers Stay Quit effects on:Composition and structure of participants’ personal networks.Characteristics of participants’ personal networks over the course of the study (eg, proportion of smokers in personal network).Spread of smoking cessation-related information, assistance, and behaviors from participants to others in their personal networks.Recipients of helping conversations report about smoking-related interactions and information exchange with participants and associated cessation-related behavior change.Aim 3: using personal network metrics derived from the personal network study (eg, size, composition, and structure), conduct mediational analyses of personal network effects on the primary and secondary study outcomes in Aim 1.

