##### Aim 1: Abstinence and Relapse

Abstinence rates at 6- and 12-months postrandomization and biochemically confirmed abstinence at 6- and 12-months postrandomization will be compared between arms using multivariable logistic regression for each outcome (6- or 12-months). Independent variables will include intervention status, strata (race and ethnicity), quitline, and covariates (as described above). We will compare time to first relapse using Cox models and Kaplan-Meier curves. The number of relapses and helping conversations will be compared between study arms using Poisson regression, with the zero-inflated Poisson or negative binomial model used if appropriate. We will carry out secondary analyses using general linear mixed models to examine change in cognitive and emotional measures of participant-reported outcomes (described above in the General Quantitative Approaches section) for participants randomized to receive Helpers Stay Quit compared to participants randomized to the usual care arm.

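### Repeat relapses are counted on a lower threshold than first relapses, so the raw number of relapses is not reliably ordered with benefit

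*Protocol article*

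**What the plan says.** Aim 1 (Research Objectives, Textbox 1) lists the number, timing and duration of "lapses and relapses to smoking (secondary outcome"), so lapses and relapses are meant to be different events.

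The section Relapse Status (Primary Outcome) and Helping Conversations (Secondary Outcome) gives two rules in consecutive sentences:

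- The threshold for a relapse comes first: "Relapse is defined as (1) any smoking on 7 consecutive days or (2) smoking at least once each week over 2 consecutive weeks".
- The rule for second and later events follows, and carries no such threshold: "Multiple relapses are defined as relapsing, reporting being quit (7-day point prevalence), and then subsequently reporting smoking again".

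For the analysis, Aim 1: Abstinence and Relapse says "The number of relapses and helping conversations will be compared between study arms using Poisson regression", with zero-inflated Poisson or negative binomial as alternatives if appropriate. Timing is handled separately: "We will compare time to first relapse using Cox models and Kaplan-Meier curves". Smoking is "assessed using a text survey weekly for the first 6 months and biweekly for months" 7 to 12 (Study Design). Re-quitting after relapse is expected under usual care: "If the client has relapsed, the quitline attempts to reengage the client in cessation services" (Quitline Usual Care Comparison).

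**The concern.** There are two linked problems.

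1. **Two thresholds for one event.** The first relapse needs sustained smoking. Later ones need only a report of smoking after a 7-day quit report. Isolated lapses are therefore promoted to relapses, but only in people who have already relapsed and re-quit. This blurs the distinction that Aim 1 draws.
2. **The count depends on re-quitting.** A participant who relapses and never stops again stays at 1 for the whole year. A participant who keeps returning to abstinence can go on accumulating events while smoking far less.

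The number of relapses is a named secondary outcome. If the intervention helps partly by getting people to re-quit, a higher count in that arm could be reported as harm. A lower count would not by itself show less smoking.

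**Working it through.** **The plan's own figures.** The document gives no figure for the relapse count. Its one calculation supplies a reference point: 25% vs 35% abstinence, 80% power, 30% dropout, chi-square test without continuity correction. With two-sided alpha 0.05 (assumed; not stated), this needs 329 per arm, and 2 × 329 / 0.70 = 940, as stated.

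**Two participants over 52 weeks.**

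- A smokes from week 5 to week 52: 48 smoking weeks, 52 − 48 = 4 abstinent weeks.
- B smokes in weeks 5 and 6, quits, then slips in weeks 12, 20 and 30: 5 smoking weeks, 52 − 5 = 47 abstinent weeks.

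| | A | B |
|---|---|---|
| Count as written | 1 | 1 + 3 = 4 |
| Count, same threshold throughout | 1 | 1 |
| Same threshold, per abstinent week | 1/4 = 0.25 | 1/47 = 0.02 |

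**Simulation, first set.** Each participant is abstinent or smoking each week for 52 weeks, with 40,000 paths per arm and no dropout. The weekly grid simplifies the biweekly texts of months 7 to 12. A relapse is two consecutive smoking weeks; as written, later relapses need one. All rates are assumptions. The columns vary the share of smoking episodes that last a single week. Ratios are intervention/control, and at-risk weeks are those not spent in a counted relapse.

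*Scenario 1: equal weekly probability of starting to smoke (0.05); weekly re-quit probability 0.015 control, 0.03 intervention.*

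| | 0% | 50% | 80% |
|---|---|---|---|
| Abstinent at week 52, control vs intervention | 0.25 vs 0.39 | 0.45 vs 0.56 | 0.69 vs 0.76 |
| Mean smoking weeks | 29.2 vs 25.4 | 19.8 vs 17.0 | 10.8 vs 9.2 |
| Count ratio as written | 1.15 | 1.13 | 1.13 |
| Same threshold only | 1.14 | 1.07 | 1.02 |
| At-risk time only | 0.99 | 1.05 | 1.09 |
| Both | 0.98 | 0.98 | 0.98 |

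*Scenario 2: start 0.05 vs 0.045; re-quit 0.015 vs 0.05.*

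| | 0% | 50% | 80% |
|---|---|---|---|
| Abstinent at week 52 | 0.26 vs 0.53 | 0.44 vs 0.69 | 0.69 vs 0.83 |
| Mean smoking weeks | 29.2 vs 20.2 | 19.9 vs 12.8 | 10.7 vs 7.1 |
| Count ratio as written | 1.21 | 1.15 | 1.09 |
| Same threshold only | 1.19 | 1.03 | 0.94 |
| At-risk time only | 0.88 | 0.95 | 1.01 |
| Both | 0.86 | 0.85 | 0.87 |

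**Hand checks.** The expected count is roughly the start probability times abstinent weeks. In Scenario 1, first column: 0.05 × (52 − 29.2) = 1.14 for control and 0.05 × (52 − 25.4) = 1.33 for intervention, against simulated means of 1.15 and 1.33. The intervention arm scores more because it is abstinent longer. With both changes the ratio should equal the ratio of rates of starting sustained smoking. That is 1.00 × 0.97/0.985 = 0.98 in Scenario 1 and 0.90 × 0.95/0.985 = 0.87 in Scenario 2, in line with the tables.

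In Scenario 1, first column, an unadjusted Poisson test at 470 per arm called the better arm significantly worse in about 78% of resamples.

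**Simulation, second set.** Separate weekly relapse and re-quit probabilities, plus 3% weekly lapses in both arms; count as written.

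| Relapse, control vs intervention | Re-quit | Count ratio |
|---|---|---|
| 3% vs 2.5% | 2% vs 6% | 1.322/1.115 = 1.19 |
| 3% vs 2.5% | 2% vs 3% | 0.99 |
| 3% vs 2.5% | 2% vs 2% | 0.90 |
| 3% vs 2% | 2% vs 3% | 0.85 |
| 5% vs 3.5% (abstinence 25% vs 35%) | 1.5% vs 1.5% | 0.86 |

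In the first row the intervention is better on week-52 abstinence (71% vs 44%) and on share of weeks smoked (23% vs 40%), yet its count is higher. With abstinence near 25% vs 37–38% and the benefit partly or wholly through re-quitting, the ratio was 1.10 to 1.22. A halved start probability (0.04 vs 0.02) with re-quit 0.02 vs 0.04 gave 0.77/1.10 = 0.70, so 0.85 is not a lower bound.

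**The case against.** **The reversal depends on the scenario.** This trial randomises people who are already abstinent and aims to prevent relapse. If the benefit comes through fewer relapses, the count points the right way, including in the scenario matched to the design's 25% vs 35%. This stands. A reader might infer that an effective intervention will look harmful. The documents do not support that; they support only that the count cannot be relied on to show the direction.

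**An exposure term may exist.** The article names no offset, and a reader might infer that none will be used. A condensed article commonly leaves offsets, exposure windows and missed-text rules to the analysis plan, so that inference is not supported. Nor can one say that dropout will simply look protective: General Quantitative Approaches plans dropout comparisons, covariate adjustment and pattern mixture models. Both objections stand. However, an offset for total follow-up would not remove the problem, because completers in both arms have the same follow-up.

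**The wording may be loose.** Smoking again may have been intended as relapsing again. That is possible, but the text does not say so, and a programmer would code what is written. A uniform threshold alone also still left ratios above 1 in most of the reversing cases.

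**Abstinent time is affected by treatment.** Using it as exposure removes credit for re-quitting: Scenario 1 gives 0.98 although the intervention arm smoked less. This stands and shapes the fix.

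**Conclusion.** The point holds in limited form. The two thresholds are in the text and do not depend on any simulation. The consequence is that the number of relapses is not reliably ordered with benefit. Under the assumed rates its ratio runs from about 0.85 (lower with a strong effect on relapse) to about 1.2 against the better arm, according to whether the intervention works mainly through fewer relapses or through re-quitting. The documents give no transition rates, so the possible change of direction is the result, not any single ratio. Neither the uniform threshold nor at-risk time is enough alone across the range.

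The damage is confined to one component of a secondary outcome. Abstinence at 6 and 12 months and time to first relapse do not use the repeat-relapse rule.

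**What to change.** 1. Apply the stated relapse definition to every relapse, first or later. Classify isolated smoking after a quit report as a lapse and count it with the lapses.
2. Analyse repeat relapses as a rate per observed abstinent time at risk, or with a recurrent-event model in which a participant re-enters the risk set on re-quitting. If the analysis plan already specifies exposure, confirm that it is abstinent time and not total follow-up.
3. Report the proportion of observed weeks smoked beside the relapse rate. This also serves the duration component of Aim 1. State that the relapse count will not be read alone as benefit or harm.
4. State a rule for weeks with no answered text and for participants with no observed abstinent time.

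The cost is definition wording and derivation code. The weekly and biweekly texts already collect smoking status, and follow-up was still running when the article was written, so this can be settled before unblinded analysis. The remaining weakness is that time at risk depends on treatment, which is why the rate and total smoking time must be presented together.

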### Sample Size, Power Estimates, and Analysis

#### Power and Sample Size for Pragmatic Randomized Controlled Trial (pRCT)

A sample size of 940 participants would yield 80% power to detect a difference in smoking cessation rates between arms of 10%, assuming a conservative control arm rate of 0.25 [65], 30% dropout, and a noncontinuity corrected *χ*^2^ test. This difference is smaller than that found in the preceding pilot feasibility study (difference=46%); this effect size was chosen as a clinically significant difference with public health implications and is feasible, given the pilot results. This sample size also yields 90% power to detect standardized effect sizes for continuous secondary outcomes of Cohen *d*=0.26, a small-to-medium effect size, and considered to be a good estimate for a minimum important difference for patient-reported outcomes.

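### As written, a first relapse needs sustained smoking but a further relapse needs only a report of smoking, so the number-of-relapses outcome can mix relapses with single lapses

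*Protocol article*

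**What the plan says.** The section on relapse status and helping conversations gives two consecutive rules. The first is the relapse definition: "Relapse is defined as (1) any smoking on 7 consecutive days or (2) smoking at least once each week over 2 consecutive weeks". The second is the rule for more than one relapse: "Multiple relapses are defined as relapsing, reporting being quit (7-day point prevalence), and then subsequently reporting smoking again".

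Textbox 1, under Aim 1, lists as a secondary outcome "The number, timing, and duration of participants’ lapses and relapses to smoking (secondary outcome"), so lapses and relapses are named as different events. The article does not define a lapse.

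The Aim 1 analysis section uses the count directly: "The number of relapses and helping conversations will be compared between study arms using Poisson regression", with zero-inflated Poisson or negative binomial models as alternatives. Time to first relapse is analysed separately with Cox models and Kaplan-Meier curves.

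The reports come from text surveys. The compensation list under Ethical Considerations gives "weekly text survey (24 total; US $4 each") for the first six months and "biweekly text survey (12 total; US $4 each") for months 7 to 12.

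**The concern.** The two rules set different thresholds. Someone who has not yet relapsed and smokes one cigarette in an otherwise smoke-free stretch has not relapsed. Someone who has relapsed once, reports 7 smoke-free days and then smokes one cigarette has, on the words of the second rule, relapsed again. The distinction that Textbox 1 draws between lapse and relapse disappears after the first relapse.

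A count model compares numbers of like events. If the event changes meaning after its first occurrence, the total reflects both how often people return to sustained smoking and how often relapsers re-quit and slip. A participant who keeps trying to quit can then score worse than one who goes back to smoking every week. The negative binomial option allows for extra variance and the zero-inflated option for extra zeros. Neither corrects an event whose definition shifts.

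**Working it through.** **The plan's own figures.** The article states no expected relapse count, so there is none to reproduce. Its one sample-size calculation does not use relapses. It is based on abstinence proportions of 0.25 and 0.35, "assuming a conservative control arm rate of 0.25 [65], 30% dropout, and a noncontinuity corrected" chi-squared test. With two-sided alpha 0.05 (my assumption; the article does not state it) and 80% power:

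n per arm = [1.960 × √(2 × 0.30 × 0.70) + 0.842 × √(0.25 × 0.75 + 0.35 × 0.65)]² / 0.10² = (1.270 + 0.542)² / 0.01 ≈ 329.

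Allowing for 30% dropout, 329 / 0.70 = 470 per arm, or 940 in total. This matches the article and does not depend on the point raised here.

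**Scoring the two rules.** Inputs: the two rules above and the 24 weekly texts. Assumptions: in each week marked as smoking, the participant smokes at least once but never on 7 consecutive days, so only the two-week criterion can be met. A week without smoking counts as a report of 7-day abstinence.

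- *As written:* the first relapse is scored at the second of two consecutive smoking weeks. After that, each smoking week that follows a smoke-free week adds one.
- *Sustained throughout:* every relapse, first or later, needs two consecutive smoking weeks, with a smoke-free week between relapses.
- *Single report throughout:* every smoking week that follows abstinence counts.

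| Weeks with smoking | Number of weeks | As written | Sustained throughout | Single report throughout |
|---|---|---|---|---|
| 1, 2, 4 | 3 | 2 | 1 | 2 |
| 2 to 24, every week | 23 | 1 | 1 | 1 |
| 1, 2, 4, 6, ..., 24 | 13 | 12 | 1 | 12 |
| 1, 3, 5, ..., 23, 24 (previous row reversed) | 13 | 1 | 1 | 12 |
| 2, 4, 6, ..., 24 | 12 | 0 | 0 | 12 |

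Row 1: relapse at week 2, quit report at week 3, smoking at week 4. The total is 1 + 1 = 2 as written. Under the sustained rule week 4 is a lapse and the total is 1.

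Row 2: relapse at week 3 and no quit report afterwards, so 1 under either rule. Row 1 has 3 smoking weeks and scores higher than row 2, which has 23.

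Row 3: relapse at week 2, then one more at each of weeks 4, 6, ..., 24. That is (24 − 4) / 2 + 1 = 11 further events and 12 in total. This assumes that the second rule recurs after each quit report. If each third or later event needs a fresh sustained relapse, the total is 2, which is still not 1.

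Row 4: the same number of smoking weeks in reverse order scores 1, because the two consecutive weeks come last.

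**The case against.** The best defence is that relapse is defined in the sentence immediately before, and the second sentence exists only to say what separates one relapse from the next, namely a 7-day quit report. On that view, smoking again is shorthand for meeting the definition again and there is one threshold. This reading is plausible, and nothing in the article rules it out. Equally, nothing states it, and an analyst who follows the words will score on the lower threshold. If the shorthand was intended, writing it out costs nothing.

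It can also be said that a journal article leaves episode-counting detail to the full protocol or analysis plan. That would answer a complaint about missing detail. Here the article does give a counting rule, and the rule departs from the definition beside it.

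Three objections about size do stand.

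- A reader might infer from rows 3 and 5 that identical smoking scores 12 or 0. It is not identical: 13 smoking weeks against 12, with two consecutive weeks in one pattern and none in the other. On the shared weeks 3 to 24 the contrast is 11 against 0. Part of the gap comes from the first-relapse definition, since the two patterns still score 1 and 0 when one sustained threshold is used.
- The 12 rests on the rule recurring, which the sentence does not spell out. The clear literal case is row 1, 2 against 1.
- These are hand-built patterns over the 24 weekly texts. They say nothing about how common such patterns are and do not score months 7 to 12.

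**Conclusion.** The inconsistency is in the text and should be corrected. Read literally, the number-of-relapses outcome combines sustained relapses with single slips after a re-quit. The smallest clear example is 2 relapses instead of 1 for a participant who smokes in only three of 24 weeks. The largest shown is 12 instead of 1, a constructed extreme that depends on repeated application of the rule and is not an expected value.

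A reader might go further and infer that the arm comparison is biased or reversed, for instance if relapsers in the intervention arm re-quit more often and so accumulate slips. The mechanism is possible, but the article gives no data on re-quitting or slip frequency in either arm, and the rule is the same in both. Neither direction nor size can be derived.

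The scope is narrow. Point-prevalence abstinence does not use the relapse definition, time to first relapse uses only the first threshold, and the sample size of 940 rests on abstinence proportions. The point concerns one component of a secondary outcome.

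**What to change.** Replace the sentence on multiple relapses with wording such as: a second or later relapse is counted only when, after a report of 7-day abstinence, the participant again meets criterion (1) or (2) of the relapse definition; any other smoking after a re-quit is counted as a lapse.

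Add a statement of how criterion (2), which needs smoking in each of two consecutive weeks, is scored from the biweekly texts in months 7 to 12. The consistent rule cannot be applied uniformly over 12 months without it.

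Apply both to the number-of-relapses analysis, and fix them before the arms are compared. The article reports that the trial is ongoing, with 12-month follow-up incomplete at submission.

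The cost is a short change to the definition, the biweekly scoring rule and the matching derivation code. The threshold change itself uses reports already being collected and needs no new procedure for participants.
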